**3.3. Selection of STIs/BV for each objective**

See Appendix Table 3 for available STI/BV data in selected studies.

For objective 1, prevalence will be estimated for six STIs/BV (chlamydia, gonorrhea, syphilis, trichomoniasis, BV, and HSV-2) based on availability of data. For the majority of studies, HPV data were not available.

For objective 2, incidence will be estimated for five of the selected STIs (chlamydia, gonorrhea, syphilis, trichomoniasis, and HSV-2). BV was not included due to concerns about the accuracy of diagnostic criteria to assess incidence given the intervals between follow-up tests.

**3.4. Definition of prevalence and incidence**

Prevalent STI/BV infections will be defined by diagnosis at the baseline visit. Infections will be coded as positive, negative, or missing/not classifiable/not collected or asked. Positive syphilis cases will be further categorized based on rapid plasma regain (RPR) titer testing as high titer active infection, low titer infection or unknown RPR titer infection.

Infections defined as:

Chlamydia: Positive: Positive nucleic acid amplification test (NAAT), enzyme immunoassay (EIA), or hybrid capture test

Gonorrhea: Positive: Positive NAAT, or culture

Trichomoniasis: Positive: Positive NAAT, InPouch culture, or wet mount

HSV-2: Positive: Positive type-specific serologic test

BV: Positive: Nugent score (≥7), Ison-Hay grade (≥Grade III), or Amsel criteria (≥ 3 criteria)

Syphilis (see Appendix table 4):

Positive (overall): positive RPR AND positive treponemal test (*Treponema pallidum* hemagglutination assay [TPHA], *Treponema pallidum* particle agglutination assay [TPPA] or Determine TP rapid test)

With subclassification based on RPR titer testing:

Positive, high titer active infection: positive RPR with a titer ≥1:8 AND positive treponemal test

Positive, low titer infection: 1) positive RPR with a titer <1:8 AND positive treponemal test

Positive, unknown RPR titer infection: 1) positive RPR with missing titer AND positive treponemal test

Negative: 1) negative RPR or 2) positive or missing RPR AND negative treponemal test

Missing: 1) positive RPR AND missing treponemal test or 2) missing RPR AND missing or positive treponemal test

For estimation of incident infections, individual study protocols will be reviewed to assess time frames of repeat STI testing, types of laboratory tests used, treatment information for curable STIs. For chlamydia, gonorrhea, trichomoniasis, and HSV-2, incident infection will be defined as the first positive laboratory test following a previously negative result for the infection. For trichomoniasis, incidence estimations will be limited to those studies where *T. vaginalis* testing was done using InPouch or NAAT. For syphilis incidence, using the categories defined above, an incident infection will be defined as:

1. participants who are negative at baseline who are diagnosed at a follow-up visit with a positive infection OR
2. participants who had a positive, low titer infection at baseline who are diagnosed at follow-up with a positive, high titer active infection with a 4-fold increase in titer.

For all analyses, time of infection will be estimated as the midpoint between the last negative test and the first positive test.

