**3.6. Stratification of prevalence and incidence estimates**

Because of possible heterogeneity in STI/BV prevalence and incidence among studies, for each STI/BV we plan to stratify results according to pre-specified characteristics. (See Supplemental Tables 1.1 – 1.2 for proposed stratifications for prevalence estimates and Supplemental Tables 2.1 – 2.2 for proposed stratifications of incidence estimates.) We will first stratify according to the study-level characteristics for region and population type. Within these strata (region and population type), we will then explore STI/BV prevalence and STI incidence according to individual-level characteristics, including: age, time period of enrolment, and pregnancy status (prevalence estimates only). Additional stratifications, such as by sexual behaviors including number of recent sexual partners, could be explored if resources allow. Additionally, diagnostic test used can influence observed prevalence. For BV, those diagnosed by Nugent or Ison-Hay criteria will be evaluated separately from those diagnosed by Amsel criteria only. A sensitivity analysis will be conducted to determine if the estimates remain robust if Amsel only results are included with the Nugent/Ison-Hay results (see section 5.3). For chlamydia, gonorrhea, syphilis and trichomoniasis, estimates will be evaluated by diagnostic test type to investigate robustness of estimates (see section 5.3).

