**5.3. Study limitations and sensitivity analyses**

Though this meta-analysis provides high quality individual participant data and valuable information about the prevalence and incidence of selected STIs/BV, our approach has some limitations. First, the validity of the results of the meta-analysis is dependent on the quality of the individual component studies. While the IPD meta-analysis can help avoid problems associated with the analyses and reporting of the component studies, it cannot eliminate bias due to their study design or conduct. For example, studies which recruited high-risk women will likely have higher incidence estimates. In addition, due to the variety of study designs, not all stratification subgroups may be available in all component studies. Second, as the HC-HIV meta-analysis dataset is a convenience sample of prospective longitudinal studies that were identified for an analysis of hormonal contraception and the risk of HIV acquisition, the studies included may not be representative of all populations in the regions of interest for the STI/BV analysis. Finally, it is also possible that we may be unable to recode variables appropriately across studies and may not be able to investigate all sub-classifications of interest.

We will perform the following sensitivity analyses to examine the robustness of the results of our meta-analyses:

1. Based on the type of diagnostic criteria – stratify and analyze data/studies by the following criteria :
2. For chlamydia and gonorrhea: any test vs. NAAT only
3. For BV: any test vs. Nugent/Ison-Hay only
4. Based on the assessment of the risk of bias of the component study – stratify studies with and without an identified risk of bias. Suggested stratification for incidence estimates: studies that have retention rates <80% at one year vs. studies that have ≥80% retention
5. Based on intervention arm – repeat incidence analysis excluding all intervention arms.
6. Based on length of follow-up – for calculation of incidence, stratify studies with short versus longer follow-up time periods. Suggested stratification: ≤3 months vs 3 or more months followup
7. Based on study inclusion criteria – remove studies that included diagnosis with a specific STI for study inclusion for investigation of the prevalence and incidence of other STIs (if resources allow)
8. Based on censoring criteria – for calculation of incidence do not censor at first diagnosis of STI in question (if resources allow)

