| #1 ([name]) | | Yes | | About 70% tested on every FU visit | EIA | Yes | Every FU visit | Culture | Yes | Yes including prevalent and incident HSV2 result | Focus EIA | | Yes | | Yes | Wet mount | Yes | | Some Fup visits | RPR/ TPHA | Yes | Nugent |
| #2 ([name]) | | Yes | | No | Hybrid capture GC/CT DNA assay | Yes | No | Hybrid capture GC/CT DNA assay | No | No | N/A | | Yes | | Some  FU visits | Wet mount | No | | No | N/A | Yes (subset) | Amsel and Nugent |
| #3a/b ([name]) | | Yes | | Every FU visit | NAAT | Yes | Every FU visit | NAAT | Yes | Yes including prevalent and incident HSV2 result | Focus  EIA | | Yes | | Yes | Wet mount | Yes | | Every 6 months | RPR/ TPPA/  TPHA | Yes | Amsel and Nugent |
| #4  ([name]) | | Yes | | >50% tested on FU2 (6M) Fewer tested on other FU visits | PCR | Yes | >50% tested on FU2 (6Mt)  Fewer tested on other FU visits | Culture/  PCR | Yes | Yes, only prevalent HSV2 result | ?? | | Yes | |  | ?? | Yes | |  | RPR/ TPPA/TPHA | Yes | Nugent |
| #5 ([name]) | | Yes | | At 6 and 12 months | PCR | Yes | At 6 and 12 months | PCR | Yes | At baseline and Final visit | IgG Kalon | Yes | | | No | N/A | Yes | | Some  FU visits | RPR/ TPPA | Yes | Nugent |
| #6 ([name]) | | Yes | | At 6, 12, 24 and 30 months | PCR | Yes | At 6, 12, 24 and 30 months | PCR | Yes | Yes  Had to be HSV-2 positive at baseline to join trial | IgG Kalon | Yes | | | At baseline, 6, 12, 24 and 30 months | In pouch and wet mount | Yes | | At baseline, 6, 12, 18, 24 and 30 months | RPR/ TPPA/ | Yes | Nugentand Ison Hay at baseline; Ison Hay at Fup |
| #7a/b ([name], [name]) | | Yes | | Every FU visit | PCR | Yes | Every FU visit | PCR | Yes | Yes including prevalent & incident HSV2 result | FocusELISA | Yes | | | Yes | PCR | Yes | | Final visit only | RPR/ TPHA | Yes, if symptomatic | Amsel |
| #8 ([name], [name]) | | Yes | | Every FU visit |  | Yes | Every FU visit | ?? | All ulcer+, random- | All ulcer+, random- | N/A | Yes | | |  | ?? | Yes | |  | TPPA/TPHA | Yes | Nugent |
| #9 ([name]) | | Yes | | >90% tested on FU2 (6M) & 4 (12M) Few tested on the other visits (max FU4) | ?? | Yes | >90% tested on FU2 (6M) & 4 (12M) Few tested on other visits (max FU4) | ?? | Yes | Yes including prevalent and incident HSV2 result |  | Yes | | |  | ?? | No Lab Form | |  | No Lab Form |  | Yes |

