**Table 5. Planned tables and forest plots**

| **Analysis objective** |  | **Meta-analysis output/presentation** | | | |
| --- | --- | --- | --- | --- | --- |
|  | **Analysis population** | **Baseline table** | **Heterogeneity evaluation** | | **One-stage stratified analysis and two-stage random effect analysis** |
|  |  |  | **I^2^** | **Forest plot** |  |
| **Primary** |  |  |  |  |  |
| **To evaluate the prevalence of selected STIs/BV: gonorrhea, chlamydia, syphilis, trichomoniasis, HSV-2, and/or BV** | **All studies** | **√** | **√** | **√** | **√** |
|  | **Region**: South Africa, Eastern Africa, Southern Africa | **√** | **√** |  | **√** |
|  | **Population type**: higher-risk or clinic/community-based populations | **√** | **√** |  | **√** |
|  | **Time period**: baseline data were collected prior to 2002, during 2003 to 2006 2007 or later | **√** | **√** |  | **√** |
|  | **Age**: 15-49 years, 15-24 years, 25-49 years | **√** | **√** | **√** | **√** |
|  | **Pregnancy**: pregnancy status at baseline | **√** | **√** |  | **√** |
|  | **Cross-stratum (Region, Population type, Time period, Age, Pregnancy)**^1^ | **√** | **√** |  | **√** |
| **To evaluate the incidence of selected STIs: chlamydia, gonorrhea, and HSV-2** | **All studies** | **√** | **√** | **√** | **√** |
|  | **Region**: South Africa, Eastern Africa, Southern Africa | **√** | **√** |  | **√** |
|  | **Population type**: higher-risk or clinic/community-based populations | **√** | **√** |  | **√** |
|  | **Time period**: baseline data were collected prior to 2002, during 2003 to 2006 2007 or later | **√** | **√** |  | **√** |
|  | **Age**: 15-49 years, 15-24 years, 25-49 years | **√** | **√** | **√** | **√** |
|  | **Pregnancy**: pregnancy status at baseline | **√** | **√** |  | **√** |
|  | **Cross-stratum (Region, Population type, Time period, Age, Pregnancy)**^1^ | **√** | **√** |  | **√** |
| **Secondary** |  |  |  |  |  |
| **To evaluate the prevalence of co-infections of selected STIs/BV: gonorrhea, chlamydia, syphilis, trichomoniasis, HSV-2, and/or BV** | **All studies** |  | **√** |  | **√** |
| **To evaluate the incidence of co-infections among the STIs: chlamydia, gonorrhea, and HSV-2** | **All studies** |  | **√** |  | **√** |
| **Sensitivity Analysis** |  |  |  |  |  |
| **To evaluate the prevalence of gonorrhea, chlamydia, syphilis, and BV based on the type of diagnostic criteria** | **All studies** |  | **√** |  | **√** |

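### The gonorrhea definition omits the only gonorrhea assay listed for study 2, and the trichomoniasis and syphilis test-type checks announced in Section 3.6 are not fully carried into Section 5.3 and Table 5

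*Protocol*

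**What the plan says.** **Gonorrhea.** Section 3.4 counts as positive: "Gonorrhea: Positive: Positive NAAT, or culture". The chlamydia line just above it accepts "Positive nucleic acid amplification test (NAAT), enzyme immunoassay (EIA), or hybrid capture test", so hybrid capture is named separately from NAAT. In Appendix Table 3, study 2 has baseline data for both infections, no follow-up testing for either, and one assay in both columns: "Hybrid capture GC/CT DNA assay".

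**Trichomoniasis.** For prevalence, Section 3.4 states "Trichomoniasis: Positive: Positive NAAT, InPouch culture, or wet mount". For incidence, the same section admits only studies that used InPouch or NAAT.

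**Test-type checks.** Section 3.6 says "For chlamydia, gonorrhea, syphilis and trichomoniasis, estimates will be evaluated by diagnostic test type to investigate robustness of estimates" and refers the reader to Section 5.3. The diagnostic-criteria items in Section 5.3 are "For chlamydia and gonorrhea: any test vs. NAAT only" and a matching one for BV. The Table 5 row reads "To evaluate the prevalence of gonorrhea, chlamydia, syphilis, and BV based on the type of diagnostic criteria".

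**The concern.** The gonorrhea rule and the data inventory do not fit together. One assay is acceptable for chlamydia and not listed for gonorrhea, and the protocol does not say whether that was intended. Two analysts could defend opposite handling of a large study, and the primary prevalence estimate would differ between them. Study 2 is large and enrolled only women aged 35-49, so its handling also affects the age mix of the South African and clinic/community strata.

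For trichomoniasis, the incidence restriction shows that the plan does not treat wet mount as equivalent to InPouch or NAAT, yet prevalence combines all three. The safeguard is the evaluation announced in Section 3.6. An analyst working from the Section 5.3 list and Table 5 would not produce it. Differences between studies and regions could then partly reflect which test was used.

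**Working it through.** **Inputs.** Enrolled N by study comes from Appendix Table 1, and test types come from Appendix Table 3, which is marked as still to be updated. The Table 1 column sums to 37,681, consistent with the approximately 37,000 in the Study Summary (+1.8%).

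**1. Gonorrhea: share of women affected**

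- Study 2: 4,160 women, South Africa, clinic/community-based, aged 35-49.
- All women: 4,160 / 37,681 = 11.0%.
- South Africa: 4,160 / 20,601 = 20.2%.
- Clinic/community stratum: 4,160 / 29,890 = 13.9%.

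The planned comparison of any test with NAAT only does not settle the matter as things stand, because what counts as any test depends on the Section 3.4 definition.

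**2. Where each infection's test-type check appears**

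| Infection | Section 3.6 | Section 5.3 list | Table 5 row |
|---|---|---|---|
| Chlamydia | yes | yes | yes |
| Gonorrhea | yes | yes | yes |
| Syphilis | yes | no | yes |
| Trichomoniasis | yes | no | no |
| BV | yes (separate sentences) | yes | yes |

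**3. Trichomoniasis: women by test listed**

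| Test in Table 3 | Studies | Women |
|---|---|---|
| Wet mount only | 1, 2, 3a/b, 11, 18a/b | 11,891 |
| InPouch or PCR | 6, 7a/b, 13, 16a-d | 14,743 |
| Shown as question marks | 4, 8, 9, 10, 12, 14, 15a-c, 17 | 10,069 |
| N/A | 5 | 978 |

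The groups add to 37,681. Table 3 labels its rows 16a/b and 15a/b; I take them to cover 16a-d and 15a-c. Among the 11,891 + 14,743 = 26,634 women with a known test, the wet-mount share is 11,891 / 26,634 = 44.6%. By region it is:

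- South Africa: 4,799 / 12,946 = 37%
- Southern Africa: 3,241 / 6,846 = 47%
- Eastern Africa: 3,851 / 6,842 = 56%

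**4. Illustration of size.** Assumptions that are not in the protocol: wet mount detects a fraction *s* of what InPouch/NAAT detects, true prevalence is equal in both groups of studies, and studies are weighted by N.

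Pooled / InPouch-NAAT value = (11,891 × *s* + 14,743) / 26,634

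- *s* = 0.5: 20,688.5 / 26,634 = 0.777, or 22% too low.
- *s* = 0.8: 24,255.8 / 26,634 = 0.911, or 9% too low.

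If 16c and 16d (1,150 + 5,654 = 6,804 women) are left out because the row label does not name them, the InPouch/PCR group is 14,743 − 6,804 = 7,939. The ratios become (5,945.5 + 7,939) / 19,830 = 0.700 and (9,512.8 + 7,939) / 19,830 = 0.880.

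**The case against.** **The gonorrhea omission may be deliberate.** Section 3.4 uses a different test list for each infection, Section 2 says choices depended on whether results could validly be combined across studies, and Table 3 is a provisional inventory of available data rather than a list of included data. This stands in part: the protocol does not show which reading was meant, so excluding study 2 is a legitimate choice. But the protocol does not state that exclusion anywhere, and updating Table 3 would not change the definition. A reader might also infer that one specimen is being accepted and rejected at once. Table 3 gives only an assay name, so the documents do not support that.

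**A trichomoniasis check is planned.** A reader might conclude that no test-type check exists for trichomoniasis. That goes too far: Section 3.6 is plan text and announces one. The risk-of-bias assessment in Section 3.8 asks whether appropriate tests were used and feeds a stratified analysis in Section 5.3, and Section 5.2.1.a calls for stratification or meta-regression when I² is not low. Either could pick up wet mount, though neither names it. What stands is that Section 3.6 points to a place where the check is not listed. Nor does the trichomoniasis definition conflict with Table 3, since both include wet mount.

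**The sizes are soft.** This is correct. They use enrolled N rather than numbers tested; study 17, for example, was tested only in a subset and may fail the 80% rule in Section 3.2. The planned estimate is two-stage pooling by population type, with random effects under heterogeneity, not N-weighting across all studies. More than a quarter of women are in studies whose test is unknown.

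**Conclusion.** Both points hold as inconsistencies within the protocol, and both should be repaired before analysis.

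For gonorrhea, a literal reading makes study 2 unclassifiable for prevalence, with the shares given above. Incidence is unaffected because study 2 has no gonorrhea follow-up, and the 15-24 age stratum is unaffected because of its enrolment ages. The documents show the possible loss of one study. They do not show that gonorrhea prevalence would be biased in a given direction.

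For trichomoniasis and syphilis, Section 3.6 is not matched by Section 5.3, and for trichomoniasis not by Table 5 either. The trichomoniasis consequence concerns prevalence only, because incidence is already restricted to InPouch or NAAT. The 9-22% figure illustrates what may be at stake under the assumed detection fraction of 50-80%, equal true prevalence, N-weighting, known-test women only, and row 16a/b covering 16a-d. It should not be read as a prediction of the error in the planned estimate.

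**What to change.** 1. **Section 3.4:** add hybrid capture to the gonorrhea definition. The existing comparison of any test with NAAT only then shows how much non-NAAT results, including hybrid capture, move the estimate. If the omission was deliberate, state instead that study 2 is excluded for gonorrhea, and why.
2. **Section 5.3 and Table 5:** add an item such as *Trichomoniasis prevalence: any test vs InPouch/NAAT only*.
3. **Syphilis:** make Sections 3.6 and 5.3 and Table 5 agree, either by specifying the syphilis comparison in Section 5.3 or by removing it from the other two places.
4. **Table 3:** complete the unknown trichomoniasis tests and clarify which sub-studies row 16a/b covers, so that the new comparison can be run.

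The cost is a few wording edits and one further sensitivity table from data already held, plus completing a table the protocol already says will be updated. The trade-off is that, under the first option, hybrid capture results enter the main gonorrhea estimate.

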**3.2. Inclusion and exclusion criteria of studies in the HC-HIV meta-analysis dataset for STI/BV meta-analysis**

The HC-HIV meta-analysis dataset contains data from 18 studies. For each objective, studies in the HC-HIV meta-analysis dataset will be included in the STI/BV analysis based on study design, population, and data availability for each study.

Within each objective, inclusion and exclusion criteria will be applied to each STI/BV separately.

Objective 1: To evaluate prevalence of chlamydia, gonorrhea, trichomoniasis, syphilis, HSV-2, and BV among women in sub-Saharan Africa by region, population type, age, pregnancy status, and time period.

The following types of studies in the HC-HIV meta-analysis dataset will be included:

- Measured the STI/BV at baseline as part of protocol
- Indicates laboratory test used for the diagnosis of the STI/BV
- Includes test result for diagnosis of the STI/BV
- Tested at least 80% of all participants in the study for the STI/BV or tested at least 80% of randomly selected sample of enrolled participants
- Measured important covariates

The following types of studies in the HC-HIV meta-analysis dataset will be excluded:

- Where the study design required the STI/BV diagnosis in question for study inclusion
- If >10% of those tested for the STI/BV had indeterminate test results

Objective 2: To evaluate incidence of chlamydia, gonorrhea, syphilis, trichomoniasis, and HSV-2 among women in sub-Saharan Africa by region, population type, age, pregnancy status, and time period

The following types of studies in the HC-HIV meta-analysis dataset will be included:

- Measured the STI at two or more study visits as part of protocol
  - - Tested for chlamydia, gonorrhea, trichomoniasis, or syphilis at least every 6 months
    - Tested for HSV-2 at least every 12 months or for studies that tested at baseline and end of the study, also had retrospective interim testing at least every 12 months for participants that seroconverted at study end.
- Includes variable to indicate laboratory test used for the diagnosis of the STI
- Includes a population or sub-population that did not receive a STI prevention intervention
  - - - If the intervention in the intervention arm does not have a demonstrated or plausible chance of impact on STI incidence, participants in the intervention arm will be included.
- Protocol indicated testing all participants for STI at specific visits

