**Table 4. Categorization of syphilis results**

| 0 | | RPR Results | | | | |
| --- | --- | --- | --- | --- | --- | --- |
|  |  | **Positive & titer ≥1:8** | **Positive &**  **titer <1:8** | **Positive &**  **missing titer** | **Negative** | **Missing** |
| Treponemal test Results | **Positive** | Positive, high titer active | Positive, low titer infection | Positive, unknown titer infection | Negative | Missing |
|  | **Negative** | Negative | Negative | Negative | Negative | Negative |
|  | **Missing** | Missing | Missing | Missing | Negative | Missing |

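### With one syphilis test missing, section 3.4 keeps the woman if her other result is negative and drops her if it is positive, which lowers estimated syphilis prevalence unless almost none of the dropped women would have been confirmed

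*Protocol*

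**What the plan says.** Section 3.4 defines a case by two tests: "Positive (overall): positive RPR AND positive treponemal test". A single negative result settles the matter the other way: "Negative: 1) negative RPR or 2) positive or missing RPR AND negative treponemal test". The remainder is not classified: "Missing: 1) positive RPR AND missing treponemal test or 2) missing RPR AND missing or positive treponemal test".

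Appendix Table 4 agrees with the text cell by cell. Its row for a missing treponemal test reads "Missing | Missing | Missing | Missing | Negative | Missing", where the first entry is the row label and the only classified cell is RPR-negative. Its row for a negative treponemal test reads "Negative | Negative | Negative | Negative | Negative | Negative", so a missing RPR is also coded Negative there.

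Section 3.4 uses the same categories for incident syphilis. Section 3.2 requires that at least 80% of participants (or of a random sample) were tested, and excludes a study "If >10% of those tested for the STI/BV had indeterminate test results". It does not state that a study must have both an RPR and a treponemal result, nor that a Missing code counts as indeterminate.

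**The concern.** Whether a woman with one missing test stays in the analysis depends on her other result. If it is negative she counts in the denominator. If it is positive she leaves both numerator and denominator. Nobody with a missing test can be counted as a case. The women removed are the ones among whom cases are found, so the loss is related to the outcome.

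Prevalence and incidence of the selected STIs are the two primary objectives, and syphilis is among the infections in both. More data do not average out a bias that sits in the definition. If the share of unconfirmed positives differs between studies, it can also add to the between-study heterogeneity on which section 5.2.1.a bases the decision to pool.

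**Working it through.** The protocol states no syphilis prevalence, incidence or missing-test rate, so there is no figure to reproduce. All rates below are assumptions.

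**1. The coding.**

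| | RPR positive | RPR negative | RPR missing |
|---|---|---|---|
| Treponemal positive | Positive | Negative | Missing |
| Treponemal negative | Negative | Negative | Negative |
| Treponemal missing | Missing | Negative | Missing |

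This is section 3.4, and it matches Table 4 once the three RPR-positive titer columns are merged.

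**2. Treponemal result missing among RPR-positive women.** Let r be RPR positivity, q the share of RPR-positive women without a treponemal result, and c the confirmed fraction, taken as equal in those tested and untested.

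- True prevalence: r·c
- Estimate under the rule: r(1−q)c / (1−qr)
- Ratio: (1−q)/(1−qr)

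With r = 5%:

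| q | Ratio | Relative bias | Coded Missing (q·r) |
|---|---|---|---|
| 10% | 0.90/0.995 = 0.905 | −9.5% | 0.5% |
| 20% | 0.80/0.990 = 0.808 | −19% | 1.0% |
| 30% | 0.70/0.985 = 0.711 | −29% | 1.5% |

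The last column shows why the 10% rule is no protection. Even if Missing counts as indeterminate, the share stays far below the limit.

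**3. RPR missing instead.** If RPR is missing at random in a share m, the estimate is p(1−m)/(1−mT), with p the true prevalence and T treponemal positivity. With p = 5% and T = 9% (the 5% plus an assumed 4% who are treponemal-positive and RPR-negative):

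- m = 10%: 0.045/0.991 = 4.5%, or −9%
- m = 20%: 0.040/0.982 = 4.1%, or −19%

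The relative bias is again close to −m.

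**4. Direction.** Let c0 be the share of untested RPR-positive women who would have been confirmed. The estimate is too low whenever c0 exceeds the estimated prevalence. Take 1,000 women with r = 5%, q = 20% and c = 70% in those tested: 50 are RPR-positive, 40 have a treponemal result, 28 are confirmed and 10 are unconfirmed. The rule gives 28/990 = 2.8%. The bias reverses only if c0 is below about 2.8%.

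In the same example, imputing at 70% gives (28 + 7)/1,000 = 3.5%, the none-confirmed bound is 28/1,000 = 2.8%, and the all-confirmed bound is 38/1,000 = 3.8%. The rule therefore lands almost on the none-confirmed bound.

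**5. A study with treponemal results only.** Every treponemal-positive woman is Missing and every treponemal-negative woman is Negative, so the estimate is exactly 0%. Appendix Table 3 lists Study 8 (551 women in Appendix Table 1) with baseline syphilis data and names only treponemal tests. At an assumed 3% to 10% treponemal positivity, 17 to 55 women would be dropped and the estimate would be 0/534 to 0/496. If Missing counts as indeterminate, the study is excluded only above 10% positivity, that is, with more than 55 of 551 women.

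**6. Incidence.** Assume 2 per 100 person-years, six-monthly visits for two years, and a share m of confirmations missing at random.

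| m | Events lost, never redetected | Events lost, still positive and retested |
|---|---|---|
| 5% | 5% | 1.3% |
| 10% | 10% | 2.7% |
| 20% | 20% | 6.2% |

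**The case against.** The strongest reply is that the codes follow from the definition. If a case needs two positives, one negative settles it and one positive leaves it open. In an RPR-first study with treponemal tests only on reactive samples, coding RPR-negative women as Negative is necessary. This stands, and no Negative code needs to change where both tests were in the algorithm. What remains is how the unconfirmed positives are handled, and dropping them is not neutral.

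Four stronger readings are tempting but unsupported.

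- A reader might infer that the bias always runs downward. It does so only if the unconfirmed positives would have been confirmed at a rate above the estimated prevalence. If missing confirmations were concentrated almost entirely in women who would have tested negative, it would reverse.
- A reader might infer that syphilis prevalence in this dataset is understated by 10 to 30%. No study's share of unconfirmed positives is documented, and it may be near zero.
- A reader might infer that Study 8 will enter at 0%. Table 3 is marked as still to be updated, and the Study 8 row has blanks or question marks for several other tests. Section 3.2 also requires a test result for diagnosis of the infection, which could be read as barring a treponemal-only study. The text does not say so.
- A reader might infer that incident cases are lost outright. Some would only be delayed to a later visit.

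The protocol also has safeguards: two reviewers consider missing data and the suitability of tests (section 3.8), results are stratified by risk of bias (section 5.3), and syphilis is to be examined by test type (section 3.6 and Table 5). These might expose a zero-prevalence study, but they do not return dropped positives to the estimate, and about 1% of women coded Missing would hardly draw attention. Imputation detail could be left to an analysis plan, but the coding rule itself is fixed in the protocol.

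**Conclusion.** The point holds in this form. Section 3.4 and Table 4 remove women with one missing syphilis test only when the available test is positive. Prevalence among classifiable women is then too low by about the share of positives lacking the second test. The percentages above assume that untested positives resemble tested ones. The downward direction needs much less: only that more than a very small fraction of them would have been confirmed. Where testing is complete the effect is negligible, and the actual size cannot be known from the protocol. Incidence is also lowered, by less when a missed case is redetected. Neither the 80% rule nor the 10% rule, nor any listed sensitivity analysis, corrects it. The 0% result is exact for any study with treponemal results only. Whether Study 8 is such a study is for the sponsor to confirm.

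**What to change.** In section 3.4, Table 4 and section 3.2:

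1. Keep the Negative codes for studies whose algorithm used both tests, whether RPR-first or treponemal-first with reflex testing.
2. Keep women whose only available test is positive in the denominator. Impute the second result from that study's own confirmed fraction among women with the same first result, and report none-confirmed and all-confirmed bounds. Treat follow-up visits in the same way for incidence.
3. Admit a study to the syphilis analyses only if its testing algorithm included both an RPR and a treponemal test.
4. Confirm whether RPR was done in Study 8 and update its row in Table 3.

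Two simpler repairs should be avoided. Restricting to women with both results would drop nearly all negatives in a reflex-tested study and push prevalence up. Coding every missing RPR as Missing would discard true negatives in a treponemal-first study.

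The cost is slightly wider intervals, one extra analysis step, and the loss of any single-test study from the syphilis analyses.
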